### Sample size calculation

Mean nerve signal intensity ratio data from our previous cross-sectional study of 13 controls and 9 participants with chronic WAD2 were analysed using a linear mixed model.^9^ The observed difference in means between controls and WAD2 participants was 0.0600 (SE=0.0315) for the C5–C8 roots of the brachial plexus, which was statistically significant; age was not a statistically significant covariate. The intraclass correlation coefficient of the nerve signal ratio was estimated to be 0.45. Assuming that there are eight assessments per participant (two sides × four roots), a SD of 0.1, intraclass correlation coefficient of 0.45 and a ratio of 3 participants with whiplash to one healthy control, the study would require 48 participants with whiplash and 16 controls to detect an effect estimate of 0.06 for the mean nerve signal intensity difference (80% power, 5% significance). Since in the acute stage it is estimated that only 50% of the participants with whiplash will develop chronicity,^51^ we will need to image 96 participants with whiplash and 32 controls for objective 1 (difference in neuroinflammation in the acute stage). Based on ~48 participants who have not recovered at 6 months, we would be able to fit a logistic regression model with 5–10 predictor variables for objective 2 (predictive factors of chronicity).

For objective 3 (development of neuroinflammation over time), we will ask 25 participants who have recovered and 25 participants who have not recovered to return at 6 months, which will enable an effect size of 0.9 to be detected using analysis of covariance, with 95% power for 5% significance. This value assumes that the correlation between the acute and chronic measurements is 0.5.

For objective 4 (validity of low cost tests of neuroinflammation), with nine independent variables, a rule of thumb for a multiple linear regression (ie, 10 participants per additional variable) implies that data from 90 participants with whiplash should be adequate to explore this.^52^

For the substudy, 68 participants with whiplash and 34 healthy controls (80% power, 5% significance, 0.53 effect size, one-tailed test) would allow the detection of a 20% smaller difference in intraepidermal nerve fibre density in the acute stage compared with healthy controls based on our previous cohort of patients with chronic WAD2.^53^

Previous longitudinal studies on WAD2 have demonstrated a <15% dropout rate over 6 months,^54 55^ and therefore we will recruit 115 participants with acute WAD2 and 34 healthy control participants.

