### Statistical analysis

Data will be exported to Stata (V.17, StataCorp, Texas, USA) for analysis. The distribution of the data will be checked for normality, and parametric, or non-parametric methods will be used as appropriate. Participants’ characteristics will be described at all time points.

For objective 1, regression analysis, or non-parametric tests, will be used as appropriate to identify differences in MRI parameters (T2-weighted STIR 4 nerve roots per side, nerve morphology and DTI parameters) and clinical tests (eg, neuropathic pain scores, tests of nerve mechanosensitivity, QST and serum inflammatory markers) between participants with acute WAD2 and age/gender-matched controls. Regression analysis will be used to assess associations with age and height.

For objective 2, recovery of participants with WAD2 will be determined at 6 months with the Neck Disability Index and a global recovery question. The analysis will be conducted with three models using different predictors measured in the acute stage: (a) MRI parameters of neuroinflammation, (b) clinical parameters that reflect neuroinflammation and (c) the addition of MRI to clinical parameters to determine whether this improves predictive strength. The dependence between MRI and clinical assessments will be investigated and composite measures added to the model. In addition, a linear regression will be performed of Neck Disability Index scores on measures of neuroinflammation.

For objective 3, mixed effects modelling will be used to compare MRI and clinical measures between recovered and non-recovered participants with WAD2 over time.

For objective 4, multivariable regression will be used to investigate the relationship of each MRI variable with the clinical parameters of neuroinflammation. In addition, a regression analysis will be performed between clinical measures of neuroinflammation and MRI parameters.

For the substudy, independent t-tests or non-parametric alternatives will be used to compare dermal and intraepidermal nerve fibre density in skin biopsies in patients in the acute phase after whiplash injury with healthy controls. Separate regression models will be used to investigate whether changes in nerve fibre density in the acute stage predict pain persistence at 6 months.

Data reduction techniques (eg, principal components analysis) may be used prior to regression modelling.

Missing data will be managed with multiple imputation strategies.

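### Objective 1's 96 + 32 does not follow from the plan's own dilution argument: if only the later-chronic half carries the 0.06 shift, power is about 53%, not 80%

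*Protocol article*

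**What the plan says.** All of the planning figures are in the protocol article, Sample size calculation. A linear mixed model of 13 controls and 9 people with chronic WAD2 gave a mean difference of 0.0600, reported as "SE=0.0315) for the C5–C8 roots of the brachial plexus, which was statistically significant". The calculation takes this value forward, using "a SD of 0.1, intraclass correlation coefficient of 0.45 and a ratio of 3 participants with whiplash to one healthy control" and eight root measurements per person, and arrives at 48 whiplash participants and 16 controls "to detect an effect estimate of 0.06 for the mean nerve signal intensity difference (80% power, 5% significance").

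The next step gives as its reason that in the acute stage "only 50% of the participants with whiplash will develop chronicity", and concludes that "we will need to image 96 participants with whiplash and 32 controls for objective 1". Allowing for dropout over six months, recruitment is set at 115 and 34.

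Under Objectives, the first objective is a cross-sectional comparison of patients within four weeks of injury with healthy controls. Under Statistical analysis, the objective 1 comparison is "between participants with acute WAD2 and age/gender-matched controls". Neither section restricts it to participants who later fail to recover.

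**The concern.** The 0.06 comes from people with chronic WAD2. If only half of an acute cohort resembles them, and the whole cohort is compared with controls, the effect is diluted. Required sample size varies with the inverse square of the effect, so halving the effect calls for four times the sample. Doubling is the right adjustment for a different purpose: ensuring that about 48 later-chronic participants are present. That serves objective 2, or a contrast confined to those participants, but the text attaches the doubled number to objective 1.

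This is the study's first objective. If the 80% is taken at face value, a null result could be read as good evidence against neuroinflammation in acute WAD2, when the chance of detecting it may have been little better than even. The effect that drives the calculation is also presented as firmer than its own standard error allows.

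**Working it through.** **Inputs (Sample size calculation).** Difference 0.06; SD 0.1; ICC 0.45; 8 measurements per participant; 3:1 ratio; 80% power; 5% significance. Sidedness is not stated for this calculation.

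**Reproducing the plan's figure.**
- Design effect = 1 + 7 × 0.45 = 4.15.
- SD of a participant's mean = 0.1 × √(4.15/8) = 0.0720.
- Controls needed = (1 + 1/3) × [0.0720 × (1.960 + 0.842)/0.06]² = 15.08, rounded up to 16, with 48 whiplash. This matches the plan.
- Power at 48/16 is 81% (noncentral t) or 82% (normal approximation).
- A one-sided test would give 12 controls, and ignoring the repeated measurements would give 30. The plan's calculation is therefore two-sided with clustering.

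**Diluted effect.** Let f be the fraction of the chronic shift that recoverers show in the acute stage. With half the cohort becoming chronic, the mean difference is 0.06 × (0.5 + 0.5f). The standard error is 0.0720 × √(1/96 + 1/32) = 0.0147 at 96/32, and 0.0720 × √(1/115 + 1/34) = 0.0141 at 115/34. Two-sided power (noncentral t):

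| f | Mean difference | Power at 96/32 | Power at 115/34 |
|---|---|---|---|
| 0 | 0.0300 | 53% | 56% |
| 0.25 | 0.0375 | 72% | 75% |
| 0.5 | 0.0450 | 86% | 89% |
| 1 | 0.0600 | 98% | 99% |

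At f = 0 the whiplash group is a mixture. Its SD rises to √(0.0720² + 0.5 × 0.5 × 0.06²) = 0.0780, and power at 96/32 falls slightly, to 51%.

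**Sample needed at f = 0.** Controls = (4/3) × [0.0720 × 2.802/0.03]² = 60.3, rounded up to 61, with 183 whiplash.

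**Difference detectable with 80% power.** About 0.042 at 96/32 and 0.040 at 115/34. Solving 0.06 × (0.5 + 0.5f) for these values gives f of about 38% and 32%.

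**Later non-recovered participants against controls.** For 48 v 32 at 0.06, the SE is 0.0720 × √(1/48 + 1/32) = 0.0164 and power is 95%. The 48 is consistent with planned dropout: 115 × 0.85 ≈ 98, of whom half is 49.

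**Pilot estimate.** 0.0600/0.0315 = 1.905. Two-sided p = 0.057 (normal) or 0.071 (t on 13 + 9 − 2 = 20 df). The 95% CI is 0.0600 ± 2.086 × 0.0315 = −0.006 to 0.126 on 20 df, or −0.002 to 0.122 by normal approximation. Rounding does not explain it: 0.06005/0.03145 = 1.909, p = 0.056.

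**The case against.** The strongest reply is that the plan never says recoverers have no acute shift. Objective 3 follows neuroinflammation over time in both recovered and non-recovered patients, which is compatible with early inflammation that later resolves in those who recover. If recoverers carry about 38% or more of the chronic shift, 96/32 reaches 80%. This stands as a limit on the finding. A reader might infer that objective 1 simply has 53% power; the documents do not support that, because 53% is the case in which recoverers show nothing. It does not rescue the calculation, however. If recoverers carried the full shift, 48 + 16 would already be enough, so a dilution is the only thing that explains inflating the sample for objective 1. No partial effect is stated that would make doubling the right amount.

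A second reply is that six-month dropout does not remove baseline scans, so the relevant numbers are 115/34. That is correct, but it moves 53% only to 56%.

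A reader might also put the required sample at 192 + 64, four times 48 + 16. That multiplies numbers already rounded up and gives 82% power; 183 + 61 is enough for 80%.

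On the pilot, the test used and its sidedness are not stated, and a one-sided normal test would give p = 0.028. But the 48 + 16 reproduces only as two-sided, and the substudy calculation declares its one-tailed test explicitly. The two figures printed do not support significance at two-sided 5%. That is not a judgement on the cited study's own analysis, which is not available here.

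**Conclusion.** The sample size for objective 1 is wrong as written: 96 + 32 does not give 80% power for the comparison described under the assumption that motivates the doubling. In the zero-effect case for recoverers, power is 53% at 96/32 and 56% at 115/34. Over the full range of possible effects in recoverers it runs from 53% to 98% at 96/32, crossing 80% at about 38%. These figures rest on the plan's own SD, ICC, number of measurements and 50% chronicity, on a two-sided 5% test, and on a shift of 0.06 in the acute stage among those who become chronic.

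The description of the pilot difference as significant is a separate misstatement and does not depend on the dilution assumption.

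It might also be inferred that the study must recruit more. That does not follow: what has to change is the stated power and the effect the study claims to be able to detect.

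**What to change.** 1. In Sample size calculation, state the acute effect assumed in participants who recover. Give objective 1 power over a range of that effect for both 96/32 and 115/34, and state the difference detectable with 80% power (about 0.042 and 0.040).
2. Keep the comparison of all acute participants with controls as objective 1. Pre-specify later non-recovered participants against controls as a secondary contrast, within the regression approach already named for objective 1 and using the recovery status already planned at six months. With 48 v 32 it has about 95% power for 0.06. Say plainly that it conditions on the six-month outcome and loses those who drop out, so it does not replace the cross-sectional question.
3. Remove the claim of statistical significance for the pilot difference and give the estimate with its 95% CI: about −0.006 to 0.126 on 20 df (−0.002 to 0.122 by normal approximation).

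The cost is rewording and one added contrast on data the study will hold anyway, with no extra participants or scans. The stated power for the first objective will look less favourable.

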## Methods and analysis

### Objectives

The first objective of this study is to determine the presence of peripheral neuroinflammation during the acute stage following a WAD2 injury. This objective will use MRI to assess the extent of peripheral neuroinflammation and nerve microstructure in a cross-section of patients within 4 weeks of injury and healthy controls. The second objective will determine whether the presence of peripheral neuroinflammation in the acute stage can predict patient recovery status at 6 months. The third objective will determine the course of peripheral neuroinflammation from the acute to chronic stages of a WAD2 injury. For this objective, we will examine changes in MRI measures and clinical tests from baseline to 6 months in both recovered and non-recovered patients. The fourth objective will determine whether low-cost clinical tests can serve as markers to detect neuroinflammation as determined on MRI. The objective of the substudy is to determine whether the structural integrity of cutaneous nerve fibres is altered in the acute stage following a WAD2 injury, and whether it contributes to the progression to chronicity.

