#### Follow-up

All participants will be asked to complete the questionnaires and answer a self-rated global recovery question 6 months after their injury. Twenty five participants who have recovered and 25 who have not recovered will undergo the full protocol. To promote participant retention, a newsletter will be sent to participants to keep them up to date about the study, and a small payment will be given to those who return their completed questionnaires at 6 months or attend their follow-up appointment.

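### Objective 3 is powered for ANCOVA but analysed as change over time between recovery groups; a group-by-time test has about 88% to 93% power for the stated effect, not 95%

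*Protocol article*

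**What the plan says.** The Protocol article describes objective 3 in three places.

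- **Objectives:** "we will examine changes in MRI measures and clinical tests from baseline to 6 months in both recovered and non-recovered patients".
- **Sample size calculation:** the follow-up sample is set as a target for each recovery group: "we will ask 25 participants who have recovered and 25 participants who have not recovered to return at 6 months". The power claimed for that sample follows, in a clause that names the method: "which will enable an effect size of 0.9 to be detected using analysis of covariance, with 95% power for 5% significance". The section adds: "This value assumes that the correlation between the acute and chronic measurements is 0.5".
- **Statistical analysis:** "mixed effects modelling will be used to compare MRI and clinical measures between recovered and non-recovered participants with WAD2 over time".

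Two further statements bear on how the groups arise. Under Statistical analysis, for objective 2, "recovery of participants with WAD2 will be determined at 6 months with the Neck Disability Index and a global recovery question". Under Objectives, objective 2 itself asks "whether the presence of peripheral neuroinflammation in the acute stage can predict patient recovery status at 6 months".

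The article does not say which term of the mixed model is tested, how baseline is handled, or whether baseline scans of participants who do not return enter the model.

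**The concern.** The power statement names one method and the analysis section names another. With randomised groups this would matter little, because the expected baseline means are equal and ANCOVA and a comparison of change estimate the same difference. Here the groups are formed by 6-month outcome. Objective 2 asks whether acute neuroinflammation predicts that outcome, so equal baseline means cannot be presumed.

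Two things are at stake. First, the natural reading of the planned analysis is less precise than ANCOVA at the same sample size, so the stated 95% does not describe it. Second, with the contrast left open, the team could choose between two different quantities after seeing the data. Only one of them, the difference in mean change, corresponds to the question about course over time.

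**Working it through.** **Inputs, all from Sample size calculation:** n = 25 per group, effect d = 0.9, correlation r = 0.5, 5% significance. Sidedness is not stated for this objective. Two-sided is assumed, and it is the reading that reproduces the stated power. The SD at a single occasion is set to 1.

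**1. The plan's own figure (ANCOVA).**
Residual SD = √(1 − r²) = √0.75 = 0.866.
Noncentrality = 0.9 / (0.866 × √(2/25)) = 3.67.
Power by noncentral t with 47 df = 94.9% (normal approximation 95.7%). The stated 95% is reproduced.

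**2. Group-by-time contrast, 25 + 25 complete pairs.**
SD of change = √(2(1 − r)) = √1 = 1.0.
Noncentrality = 0.9 / (1.0 × √(2/25)) = 3.18.
Power by noncentral t with 48 df = 87.7% (normal approximation 88.9%).
At r = 0.5 the SD of change equals the single-occasion SD, so it does not matter which of the two standardises the 0.9.
The effect detectable with 95% power is 1.04 SD by noncentral t (1.02 by the normal formula).

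**3. Dependence on the correlation (noncentral t, 25 + 25).** Both methods are shown at each r, so that the effect of the method is not confused with the effect of r.

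| r | ANCOVA | Group-by-time |
|---|---|---|
| 0.3 | 90.4% | 75.0% |
| 0.4 | 92.5% | 81.2% |
| 0.5 | 94.9% | 87.7% |
| 0.6 | 97.4% | 93.6% |
| 0.7 | 99.2% | 98.1% |

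**4. Group-by-time using all available baseline scans.** With N baselines and 25 follow-ups per group, the variance of the estimated mean change in one group is (1 − r²)/25 + (1 − r)²/N, which is 0.75/25 + 0.25/N at r = 0.5. The article does not give N for this purpose. The assumed range is 48 (half of the 96 to be imaged) to 57 (about half of the 115 recruited).

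- N = 25 (returners only): variance 0.0400, power 88.9%.
- N = 48: variance 0.0352, power 92.4%.
- N = 57: variance 0.0344, power 92.9%.

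These three use the normal approximation, so the gain should be read against 88.9%, not 87.7%.

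**5. What ANCOVA estimates when baselines differ.** Let the baseline difference be b and the difference in mean change be c. The follow-up difference is b + c. ANCOVA with slope r estimates (b + c) − r·b, which is c + 0.5b at r = 0.5. For illustration, b = 0.5 SD moves the ANCOVA estimate 0.25 SD away from the difference in change, even if both groups change equally. A mixed model that constrains the baseline means to be equal has the same property.

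**The case against.** The strongest reply is that nothing has been miscalculated. The 95% is correct for the method it names, and a journal article may leave the exact model to a fuller document. The analysis section names neither the tested term nor the analysis set, so 88% rests on two inferences: that the test is group-by-time, and that only complete pairs are used. A likelihood-based mixed model uses incomplete pairs unless told otherwise, and nothing restricts it to the 50 returners, which would put power at about 92% to 93%. A baseline-adjusted mixed model would return about 95%. Even the lowest of these, at the plan's own r = 0.5, exceeds the 80% used for objective 1 and the substudy.

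Most of this stands, and it rules out three stronger readings.

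- A reader might infer that power is simply 88% rather than 95%. The text does not fix the specification that this requires, and the two methods do not target the same effect when baselines differ.
- A reader might infer that power is likely to fall below 80%. That needs a correlation below 0.4. The plan assumes 0.5, and a higher correlation raises power just as readily. Nor does the article give a basis for assuming fewer than 25 usable pairs per group: it says that "Twenty five participants who have recovered and 25 who have not recovered will undergo the full protocol".
- A reader might call ANCOVA biased here. It is more exact to say that it estimates a different quantity, the 6-month difference given baseline.

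The reply does not remove the mismatch. Both methods are stated in the article, so this is not detail left to an unseen plan. The objective is worded as change from baseline, which makes group-by-time the natural reading, and the only specifications that recover 95% are those that fit poorly with outcome-defined groups.

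**Conclusion.** The point holds as a mismatch between the power statement and the planned analysis, not as an arithmetic error. If objective 3 is tested by the group-by-time contrast without an equal-baseline constraint, power for 0.9 SD at r = 0.5 (two-sided 5%) is about 88% with the returners alone, or about 92% to 93% with all baseline scans of participants whose recovery status is known. The second range rests on the assumed 48 to 57 baselines per group. The shortfall against the stated 95% is therefore roughly 2 to 7 percentage points. The returners-only figure is sensitive to the correlation: 81% at r = 0.4 and 94% at r = 0.6. The consequence is moderate. The stated figure should be corrected and the contrast fixed in advance, but the design remains adequate at the plan's own correlation.

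**What to change.** In the statistical analysis section, name the group-by-time term as the test for objective 3, without constraining baseline means to be equal. State that the mixed model includes the baseline scans of all participants with known recovery status, not only those who return. In the sample size section, replace the ANCOVA statement with the power of that test: at r = 0.5, 25 + 25 returners give about 88% power for a 0.9 SD difference in change and 95% for 1.04 SD, rising to about 92% for 0.9 SD if about 48 baselines per group enter the model.

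If the team does want the 6-month difference adjusted for baseline, ANCOVA and 95% can stay, but the objective and the analysis section should then say that this, and not the difference in change, is the quantity of interest.

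The cost is a few sentences. The extra baseline scans are already planned, and neither the sample size nor the visits change.

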### Statistical analysis

Data will be exported to Stata (V.17, StataCorp, Texas, USA) for analysis. The distribution of the data will be checked for normality, and parametric, or non-parametric methods will be used as appropriate. Participants’ characteristics will be described at all time points.

For objective 1, regression analysis, or non-parametric tests, will be used as appropriate to identify differences in MRI parameters (T2-weighted STIR 4 nerve roots per side, nerve morphology and DTI parameters) and clinical tests (eg, neuropathic pain scores, tests of nerve mechanosensitivity, QST and serum inflammatory markers) between participants with acute WAD2 and age/gender-matched controls. Regression analysis will be used to assess associations with age and height.

For objective 2, recovery of participants with WAD2 will be determined at 6 months with the Neck Disability Index and a global recovery question. The analysis will be conducted with three models using different predictors measured in the acute stage: (a) MRI parameters of neuroinflammation, (b) clinical parameters that reflect neuroinflammation and (c) the addition of MRI to clinical parameters to determine whether this improves predictive strength. The dependence between MRI and clinical assessments will be investigated and composite measures added to the model. In addition, a linear regression will be performed of Neck Disability Index scores on measures of neuroinflammation.

For objective 3, mixed effects modelling will be used to compare MRI and clinical measures between recovered and non-recovered participants with WAD2 over time.

For objective 4, multivariable regression will be used to investigate the relationship of each MRI variable with the clinical parameters of neuroinflammation. In addition, a regression analysis will be performed between clinical measures of neuroinflammation and MRI parameters.

For the substudy, independent t-tests or non-parametric alternatives will be used to compare dermal and intraepidermal nerve fibre density in skin biopsies in patients in the acute phase after whiplash injury with healthy controls. Separate regression models will be used to investigate whether changes in nerve fibre density in the acute stage predict pain persistence at 6 months.

Data reduction techniques (eg, principal components analysis) may be used prior to regression modelling.

Missing data will be managed with multiple imputation strategies.

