## Introduction

Whiplash injury sustained by a motor vehicle collision can cause significant long-term pain and disability. In the UK, economic costs are as high as £3 billion per year mostly due to healthcare costs.^1^ Most whiplash cases are considered whiplash-associated disorder grade 2 (WAD2), as defined by the Quebec Task Force Classification system.^2^ WAD2 refers to musculoskeletal pain and tenderness but with no frank nerve injury identified during routine clinical testing (eg, electrodiagnostic testing, neurological bedside testing). Approximately 50% of the people with WAD2 develop chronic symptoms that frequently persist for more than 5 years.^3 4^ Although a limited number of prognostic factors have been identified,^5^ they do not indicate a site of tissue pathology. This lack of understanding of the underlying pathophysiology likely explains why treatments for this condition are relatively ineffective.^6 7^ Despite the absence of a detectable nerve injury on routine clinical testing, many of the clinical features of WAD2 indicate a syndrome that is neuropathic in nature, such as reduced vibration thresholds, cutaneous thermal hypoaesthesia and cutaneous hypersensitivities to tactile and thermal stimuli distal to the site of injury.^3 8–14^ Furthermore, clinical tests of nerve trunk mechanical sensitivity, such as palpating over upper limb peripheral nerve trunks and positioning the upper limb in postures that increases the tension in the brachial plexus and median nerve (the upper limb neurodynamic test-1; ULNT1), provoke symptoms in many patients.^8 9 14^ Based on these findings, we propose that some people diagnosed with WAD2 may have an undetected nerve pathology, such as peripheral neuroinflammation, which could be a cause of chronicity. Consistent with a role for neuroinflammation, animals with a localised neuritis develop tactile and thermal-evoked cutaneous hypersensitivities in the absence of axonal degeneration.^15–17^ Of note, intact nociceptive axons become mechanically sensitive responding to pressure and stretch,^17–20^ similar to the neural mechanosensitivity observed in people with WAD2.

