#### Questionnaires

Patients will complete the following validated questionnaires: Neck Disability Index (NDI),^31 32^ pain detect questionnaire (painDETECT),^33^ short post-traumatic stress inventory (PTSD-8),^34^ Pain Catastrophising Scale (PCS),^35^ Depression, Anxiety and Stress Scale (DASS42),^36^ the quality of life questionnaire (EQ-5D-5L),^37^ and the Impact of Events Scale (IES-Revised).^38^

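### The objective 2 models, as stated, name no baseline-severity term, so they could not show that MRI adds prognostic information beyond initial disability and pain

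*Protocol article*

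**What the plan says.** The Objectives section of the protocol article sets the second objective as determining "whether the presence of peripheral neuroinflammation in the acute stage can predict patient recovery status at 6 months". In the Statistical analysis section, "recovery of participants with WAD2 will be determined at 6 months with the Neck Disability Index and a global recovery question". Three models follow, each defined by its acute-stage predictors: "a) MRI parameters of neuroinflammation, (b) clinical parameters that reflect neuroinflammation and (c) the addition of MRI to clinical parameters". The third is meant to show whether MRI improves prediction. The section then adds that "a linear regression will be performed of Neck Disability Index scores on measures of neuroinflammation". The time point of that NDI score is not given; 6 months is the natural reading, because the sentence belongs to objective 2.

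Baseline severity is measured. Under the baseline and follow-up appointment, "Patients will complete the following validated questionnaires: Neck Disability Index (NDI", and the Clinical assessment section records current symptom severity on a 0–100 mm visual analogue scale (VAS). The Follow-up section has all participants repeat the questionnaires at 6 months. The Introduction accepts that other predictors are known: "Although a limited number of prognostic factors have been identified".

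The Sample size calculation section expects about 48 non-recovered participants and allows 5–10 predictors in the logistic model.

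**The concern.** NDI is both a baseline measure and part of the outcome, yet no objective 2 model names the baseline value. Patients who start with more disability and pain can be expected to do worse at 6 months. If MRI signal also tracks initial severity, MRI will be associated with outcome for that reason alone, and the models as stated cannot separate this from information that MRI adds.

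Model (c) does not close the gap. It tests MRI against other markers of neuroinflammation, not against initial disability or pain. A positive result would leave open whether the scan tells a clinician more than a questionnaire the patient has already filled in. That matters because the study's main aim includes the role of nerve pathology in prognosis. For a continuous outcome, leaving out a strong baseline predictor also costs precision.

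**Working it through.** **1. The plan's own figures.** Events: 96 × 0.50 = 48, and as a cross-check 115 × 0.85 × 0.50 = 48.9. Events per variable: 48/10 = 4.8 to 48/5 = 9.6. The stated figures reproduce. The point concerns model content, not a wrong number.

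**2. What each model names.**
- Model (a), "a) MRI parameters of neuroinflammation": no severity term.
- Model (b), "b) clinical parameters that reflect neuroinflammation": not itemised. The nearest list, the examples of clinical tests under objective 1, includes neuropathic pain scores but neither NDI nor pain VAS.
- Model (c): the set in (b) plus MRI, so the same uncertainty applies.
- Linear regression of NDI: neuroinflammation measures named, baseline NDI not named.

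**3. How far severity alone could carry MRI in the linear model.** None of the correlations below comes from the documents. Let a be the correlation of MRI with baseline NDI and b that of baseline with 6-month NDI, with no other link from MRI to outcome. The induced correlation is r = a × b. With n = 96, z = atanh(r) × √93, and the two-sided 5% rejection rate is Φ(z − 1.96) + Φ(−z − 1.96).

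| a | b | r | MRI flagged |
|---|---|---|---|
| 0.3 | 0.4 | 0.12 | 21% |
| 0.3 | 0.5 | 0.15 | 31% |
| 0.3 | 0.6 | 0.18 | 42% |
| 0.4 | 0.4 | 0.16 | 34% |
| 0.4 | 0.5 | 0.20 | 50% |
| 0.4 | 0.6 | 0.24 | 66% |

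**4. Check by simulation, including the logistic model** (n = 96, 1,500 replicates per setting, outcome split at 50% for the logistic model, b = 0.4 and 0.6).

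| a | Linear, unadjusted | Logistic, unadjusted |
|---|---|---|
| 0 | 4–6% | about 5% |
| 0.2 | 14–23% | 9–14% |
| 0.3 | 22–42% | 15–27% |
| 0.5 | 51–83% | 35–64% |

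With baseline severity in the model, MRI is flagged in about 4–6% of studies in every setting.

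**5. Precision in the linear model at b = 0.5.** Adjustment leaves 1 − 0.5² = 0.75 of the outcome variance. If MRI is unrelated to baseline NDI, the gain is 1/0.75 = 1.33, worth about 33% more participants. Collinearity reduces it by the factor 1 − a²: 1.333 × 0.91 = 1.21 for a = 0.3 and 1.333 × 0.84 = 1.12 for a = 0.4. The gain is therefore about 12–33%. The lower end is rough, because this treats the whole outcome variance as residual before adjustment. In the scenario of step 3, MRI itself accounts for (a × b)², which is 0.0225 or 0.04, and the ratios become 0.9775 × 0.91/0.75 = 1.19 and 0.96 × 0.84/0.75 = 1.08. This argument does not carry over to logistic regression.

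**6. Effect on the predictor budget.** Reserving two of the 5–10 terms leaves 3–8 for MRI and clinical measures, with events per variable unchanged at 4.8–9.6. Adding two terms on top gives 48/12 = 4.0 to 48/7 = 6.9.

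**The case against.** The strongest reply is that objective 2 asks about prediction, not about an effect independent of initial disability. If MRI predicts outcome through severity, it still predicts outcome. The Introduction proposes neuroinflammation as a possible cause of chronicity, so baseline pain and disability may lie on the causal path, and adjustment would then remove part of the association of interest. This stands. It means that the rates in steps 3 and 4 are false-positive rates only for a claim of value beyond severity, and that the unadjusted estimate deserves to be reported in its own right.

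The second reply is that the article lists the predictors that distinguish the models without saying they are the only terms, and that covariates may be set out in an analysis plan that is not shown. This stands in part. A reader might infer that all objective 2 analyses will be unadjusted and that no severity information enters them. The text does not go that far: it does not call the sets exhaustive, and neuropathic pain scores may sit in (b) and (c). Still, the article defines the models by their content, and followed as written they contain no named severity term.

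The third reply is that the illustrative rates depend on assumed correlations, are largest for the supplementary linear regression, and fall to nominal when MRI is unrelated to severity. This also stands.

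**Conclusion.** The point holds as a gap in the stated models, clearest for model (a) and the linear regression. As written, the plan could not show that MRI adds prognostic information beyond a severity questionnaire already completed, and an association between MRI and outcome could reflect initial severity.

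The size is illustrative. In the linear model with 96 patients, MRI would be flagged in about 21–66% of studies if MRI correlates 0.3–0.4 with baseline NDI, baseline and 6-month NDI correlate 0.4–0.6, and MRI has no further link to outcome. For the logistic model the rate is about 15–27% at an MRI–severity correlation of 0.3. The precision forgone in the linear model is about 12–33% at an NDI correlation of 0.5, with the lower end approximate.

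A reader might go further and infer that an MRI finding from the planned models would be spurious. The documents do not support that: they give no correlation between MRI and severity, and an unadjusted association is a legitimate answer to the prediction question as worded.

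**What to change.** State in the objective 2 analysis that:
- the linear regression of 6-month NDI includes baseline NDI as a covariate, and the 6-month time point is named;
- the recovery models start from a base model with baseline NDI, and pain VAS if the 5–10 predictor budget allows, to which clinical markers and then MRI are added;
- adjusted and unadjusted MRI estimates are reported together, the unadjusted one read as total predictive association and the adjusted one as value beyond initial severity, with any claim of added prognostic value resting on the adjusted one.

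The clinical set in (b) should be itemised at the same time, so that its overlap with baseline pain is visible.

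The cost is wording plus one or two predictor terms on about 48 events. No new data, visits or participants are needed. The terms are better taken from within the 5–10 budget than added to it, since events per variable are already as low as 4.8. The change should be fixed before the 6-month outcomes are analysed.
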